### Patient inclusion criteria

Be aged at least 60 years.

Be taking 5 or more long-term drugs (6 months or longer).

### Patient exclusion criteria

Life expectancy less than 12 months.

### Intervention

Blinding of PCPs is not possible in this study design and even participation in a study addressing a certain topic can influence a physician’s behavior. To achieve a degree of blinding, PCPs are not provided with specific information at invitation. They will receive a lecture (length: 2 hours) about multimorbidity in general and instructions for collecting data in a usual care group. PCPs from the control group will be told that the study purpose is to investigate best practices for physician-patient communication.

PCPs in the intervention group will undergo a physicians’ training with instruction on how to use the algorithm including a communication skills training. The adapted GPGP-algorithm used in our trial consists of four steps and is a patient-centered process. First, the drugs are listed together with the four main diagnoses as well as the four main disorders from the patient’s perspective. Then the following steps will be systematically followed (see Fig. 2):

**Fig. 2 Fig2:**
[figure not shown]
Improving drug therapy in primary care (adapted from [20] and [21])

Indication of the drug in this patient (identifying undertreatment or overtreatment)Do the known possible adverse reactions of the drug outweigh the possible benefits? (Potential adverse events)Can the dosing rate be reduced with no significant risk? (Dosing problems)Is there another drug that may be superior to the one in question?

Finally, the result of this analysis will be discussed together with the patient. For each drug the PCP will note whether the patient agrees with the recommendation.

After obtaining informed consent from the patient, a practice nurse or the PCP creates a list of the patient’s present medication. Then, the PCP defines the four major clinical problems and, together with the patient, the four most important complaints from the patients’ perspective. Physicians in the intervention group then decide, for every drug listed, whether the indication is correct, whether there are side effects, whether an alternative treatment would be suitable or whether a change in the dosage is indicated (key questions of the algorithm). After discussion with the patient, the PCP and patient decide together whether to stop a drug, to change the dosage of a drug or to switch to an alternative drug, with the option to restart if symptoms should increase or the disease deteriorate.

### Primary outcomes measures

Change in the number of drugs (deprescribing rate) 12 months after applying the tool.

The primary outcome will be calculated on the basis of the medication list, provided by the practice nurse or the PCP at baseline (before the intervention) and 12 months afterwards.

### Secondary outcome measures

Table 1 displays the secondary outcomes with the appropriate measuring method.

**Table 1 Tab1:** Secondary outcomes and the appropriate measuring method

Secondary outcomes	Measuring method
1. Change in the number of drugs immediately after the encounter and 6 months later	Medication list at baseline and after 6 months
2. Reason for a change, categorized in the 4 options of the algorithm, number of drugs in each category 12 months after applying the tool	Medication list of the changed medications after the intervention, with the reason for a change
3. Discrepancy in the decision to quit, change or continue the drug between PCP and patient	Medication list after intervention with any suggestion from the PCP for a change; medication list after the intervention and after shared-decision-making
4. Number of drugs for which the patient is suggesting a change	Medication lists at baseline, after 6 and 12 months
5. Number of drugs the patient is taking not known to the PCP	Medication lists at baseline, after 6 and 12 months
6. Time consumption of the intervention	Measurement of the time through the practice nurse and the PCP
7. Disease-specific variables to evaluate the course of the disease(s) for which the patient is being treated	Symptom scores and measurements of biometric analysis (e.g. blood pressure monitoring, serum glucose) and VAS scales (e.g. pain). Event rates (hospitalization, death) and unexpected adverse event rates
8. Number of drugs readopted due to an unfavorable course of the disease(s) (readoption rate)	Medication lists at baseline, after 6 and 12 months
9. Quality of life (QoL)	Patient rating on a 5-point Likert scale
	EQ-5D-3 L at baseline, after 6 and 12 months
10. Barriers perceived by patients and PCPs against the approach/algorithm	Phone interview with the patients 13 months after intervention
11. Number of drugs which have been started	Medication lists at baseline, after 6 and 12 months

*EQ-5D-3 L* EuroQol health status measure, *PCP* primary care practitioner, *VAS* visual analogue scale

After the baseline assessment (including gender and living situation) systematic follow-up measurements will take place after 6 and 12 months.

#### Patient-reported outcomes

Quality of life (QoL) will be assessed using the EuroQol (EQ-5D-3 L). This is a generic preference-based health status measure that has been shown to be valid and reliable in a variety of populations and patients groups [22–25].

Furthermore, patients are asked to determine their QoL on a Likert scale from −2 to +2. They are asked about their main complaint and they have to indicate the intensity (no complaint to unsupportable) on a visual analogue pain scale.

#### Disease-specific parameters

PCPs of both groups measure the following disease-specific parameters at baseline, after 6 and after 12 months:Weight and blood pressureGlycated hemoglobin (HbA1c), for patients with diabetes onlyThyroid-stimulating hormone (TSH), for patients with thyroid hormone substitution onlyHemoglobin, for patients with iron substitution or vitamin B_12_ substitution only

Furthermore, the PCP evaluates the course of the main diseases (stable, improvement, aggravation).

#### Safety outcomes

Adverse events have to be reported by the PCP at the study center and the safety board. The following definition for adverse events is used:Complication of an existing disease (e.g. myocardial infarction in a coronary heart disease patient)Acute illness newly diagnosedHospitalization or death

In case of adverse events the safety board can consult the medical history of the patient and, together with the PCP, it decides whether there is a plausible connection between intervention and adverse event.

The safety board is composed of a clinical ethicist, biostatistician and a geriatrician.

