**Discussion:**

Answering the four questions of the algorithm requires a weighing-up of risks and benefits and contains a shared-decision-making approach: a prioritization of the treatment goals is necessary. This can only be done in collaboration with the patient. The majority of patients with multimorbidity are treated in the primary care setting. This underlines the significance of our study carried out in this setting: given the high prevalence of adverse drug events in patients with multimorbidity an intervention like ours has a large potential to reduce drug-related morbidity.

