### Study hypothesis

The implementation of an algorithm adapted to the GPGP leads to a reduction of polypharmacy among patients with multimorbidity (60 years and older) in a primary care setting.

Furthermore, this implementation does not worsen the quality of life or the course of the disease for which the drug was originally prescribed for (safety issues of the intervention).

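### The adverse-event definition names neither withdrawal reactions, symptom return after a drug change nor adverse drug reactions, so non-serious ones have no stated route to the safety board and no outcome counts drug or withdrawal reactions by arm

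*Protocol article*

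**What the plan says.** The Safety outcomes section sets the reporting route: "Adverse events have to be reported by the PCP at the study center and the safety board". It then fixes what counts: "The following definition for adverse events is used:Complication of an existing disease" opens a list of three items. The first item, with its example, is "Complication of an existing disease (e.g. myocardial infarction in a coronary heart disease patient"); the others are a newly diagnosed acute illness, and hospitalisation or death. For reported events the safety board may consult the patient's history and, with the PCP, "it decides whether there is a plausible connection between intervention and adverse event".

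Three other places bear on this:

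- The Study hypothesis section makes safety part of what is tested: "this implementation does not worsen the quality of life or the course of the disease for which the drug was originally prescribed for".
- The Intervention text after Fig. 2 lets PCP and patient stop, reduce or switch a drug "with the option to restart if symptoms should increase or the disease deteriorate".
- The Discussion paragraph of the Abstract says that "an intervention like ours has a large potential to reduce drug-related morbidity".

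Table 1 lists further safety-related measures, among them "Symptom scores and measurements of biometric analysis (e.g. blood pressure monitoring, serum glucose) and VAS scales (e.g. pain"), hospitalisation and death rates, rates of unexpected adverse events (a term not defined), the readoption rate and quality of life.

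**The concern.** The intervention consists of changing drugs. Its most direct possible harm is a reaction to that change: withdrawal, or return of the symptoms the drug was controlling. Its claimed advantage is less harm from drugs. The definition that triggers reporting names neither, although the Intervention text foresees symptoms increasing and the Background gives adverse drug reactions as a danger of polypharmacy.

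Two things are at stake. During the trial, the safety board may not see non-serious reactions that the PCP handles without admission or a new diagnosis. At the end, the report could not state how many patients in each arm had a withdrawal reaction or an adverse drug reaction. A conclusion that the intervention is safe, or that it lowers drug-related morbidity, would then rest on indirect measures.

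**Working it through.** The point concerns scope and wording. The plan gives no figure to reproduce, so the check sets the definition against the events of interest and then against the other measures.

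**Step 1: does the definition cover the events?**

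- *Symptom return managed in the practice* (for example, a complaint that worsens after a dose reduction and settles). It is neither a newly diagnosed illness nor an admission. It counts as a complication of existing disease only if the PCP reads that term broadly.
- *Non-serious withdrawal reaction.* It need not be a complication of the treated disease, and a PCP may not record it as a new acute illness.
- *Non-serious adverse drug reaction*, in either arm. The same reasoning applies.
- *Severe forms of all three.* These can enter as a complication, an acute illness, an admission or a death.

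The list is introduced as the definition in use and has no category for other events, so the first three depend on each PCP's interpretation.

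**Step 2: do other measures fill the gap?**

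| Measure (section) | What it gives | What it leaves out |
|---|---|---|
| Readoption rate (Table 1, outcome 8) | Drugs restarted for an unfavourable disease course | Symptoms that are tolerated, self-limiting or treated with another drug |
| Symptom scores and visual analogue scale (Table 1, outcome 7; Patient-reported outcomes) | Intensity of the main complaint; the symptom scores are not named | Symptoms other than the main complaint, as far as specified |
| Disease-course rating (Disease-specific parameters) | Three-level PCP rating of the main diseases | Reactions unrelated to those diseases |
| Weight, blood pressure, HbA1c, TSH, haemoglobin (same section) | Both arms, at baseline, 6 and 12 months | The last three are measured in subgroups only |
| EQ-5D-3L and Likert scale (Table 1, outcome 9) | Overall quality of life | Cause and timing of a change |
| Reason for change (Table 1, outcome 2) | Drugs changed under each algorithm question | Counts drugs, not reactions in patients; the algorithm is used in the intervention arm only |
| Unexpected adverse event rates (Table 1, outcome 7) | Not defined | Cannot be matched to the Safety outcomes definition |

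The Statistical analysis section provides tests for secondary outcomes, so symptom return does reach a comparison, but indirectly. No row counts adverse drug reactions or withdrawal reactions by arm. PCPs consider side effects drug by drug only as a step of the algorithm, hence in one arm. Nothing in the text sends any of these measures to the safety board.

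**Step 3: timing.** Adverse-event reporting is not tied to visits. The scheduled ratings at 6 and 12 months are, so a transient early reaction can resolve before it is rated.

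**Step 4: scale, as illustration only.** The Sample size section gives 30 clusters of 13, so 30 × 13 / 2 = 195 patients per arm, or 215 after allowance for drop-out. Suppose, purely as an assumption, that 5% to 20% of intervention patients have a reaction fitting none of the three items:

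- 195 × 0.05 = 9.75 and 195 × 0.20 = 39
- 215 × 0.05 = 10.75 and 215 × 0.20 = 43

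That is about 10 to 43 patients. The percentages have no source in the document.

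**The case against.** A reader might infer that these harms never reach the safety board or the comparison, and that there are no data on the claimed benefit. The documents do not support that.

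- **Board.** The myocardial infarction is an example, not a severity threshold. Deterioration of a treated disease can be reported as a complication, and a clinically apparent reaction as an acute illness or an admission. The board then judges the link to the intervention.
- **Comparison.** Symptom return is reflected in outcomes 7 to 9 and in the disease-course rating, and these measures match the stated safety hypothesis.
- **Benefit.** The sentence on drug-related morbidity speaks of potential and is not a hypothesis. Admissions and deaths, which the Background links to adverse drug reactions, are collected.
- **Bias.** Undercounted withdrawal harm would favour the intervention, and uncounted avoided drug reactions would work against it, so no net direction is established.
- **Article format.** Form content commonly sits in a full protocol.
- **Remedy.** Reports tied to drug changes are partly subjective, and the Intervention section says that PCPs cannot be blinded.

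The first four objections stand and limit the claim. The fifth carries less weight, because the article does more than omit form detail: it states the definition and makes it the trigger for reporting. The sixth is a real cost and belongs in the fix.

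**Conclusion.** The point holds in a limited form. The definition, as written, names neither withdrawal reactions, symptom return after a drug change nor adverse drug reactions, and has no residual category. Non-serious cases managed in the practice therefore have no stated route to the board. Adverse drug reactions and withdrawal reactions are not counted by arm, and symptom return is compared only indirectly. Severe cases are not lost.

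The number of events missed, and the direction of any bias, cannot be derived from the document; the illustration above shows scale under an assumption and is not evidence. The conclusion rests on reading the three items as exhaustive, which their introduction supports, and on there being no broader definition in a full protocol that is not shown. The primary outcome is unaffected. The gap should be closed because it concerns the safety claim of a deprescribing trial and is cheap to close.

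**What to change.** Amend the Safety outcomes definition by adding two categories:

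1. Withdrawal reaction, or return or worsening of symptoms, after any drug is stopped, reduced or switched.
2. Suspected adverse drug reaction.

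PCPs in both arms should report these when they occur, with onset date, and put one identically worded question to patients in both arms at 6 and 12 months. The visit question alone would not suffice, since it shares the timing gap of the scheduled ratings. Define the unexpected adverse event rates in Table 1 so that they agree with the amended definition. Report rates of both categories by arm, beside hospitalisation and death.

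The change affects data capture only, not treatment. It costs two entries on the case report forms, one question at two visits, and more reports for the study center and board to handle. The main drawback is that these events are partly subjective and intervention PCPs may report them more readily. The report should say so, and the less subjective hospitalisation and death rates shown alongside help the reader judge it.

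### Table 1, outcome 7 limits adverse events other than hospitalization and death to undefined unexpected ones, so some complications within the protocol's own definition can drop out of the by-arm safety comparison

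*Protocol article*

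**What the plan says.** Four places in the protocol article bear on this point.

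- **Study hypothesis.** Besides reducing polypharmacy, the trial is to show that "this implementation does not worsen the quality of life or the course of the disease" for which the drug was prescribed. The article labels this the safety side of the intervention.
- **Safety outcomes.** "Adverse events have to be reported by the PCP at the study center and the safety board". The definition has three classes: a complication of a disease the patient already has, a newly diagnosed acute illness, and hospitalization or death. Nothing in it separates expected from unexpected events, and reporting is not limited to one arm. The board may consult the patient's history and, jointly with the PCP, "it decides whether there is a plausible connection between intervention and adverse event".
- **Secondary outcome measures, Table 1, outcome 7.** The event component of the disease-course outcome is "Event rates (hospitalization, death) and unexpected adverse event rates". The same row lists symptom scores, biometric measurements and visual analogue scales.
- **Intervention.** "Blinding of PCPs is not possible in this study design". The Abstract calls the trial double blinded, and the section on PCP recruitment says that PCPs learn their group only at the end. But only intervention PCPs are trained in and apply the algorithm, so they know what was done to the medication.

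Under Disease-specific parameters, the PCP also rates the course of the main diseases in three grades.

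**The concern.** The event outcome in Table 1 is narrower than the adverse event definition it should draw on. The narrowing hangs on one undefined adjective. In a deprescribing trial, the events most directly linked to the intervention are worsening or complications of the disease whose drug was stopped, reduced or switched. Those are also the events a careful clinician would foresee, so they are the easiest to label as expected.

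If outcome 7 is followed as written, such events can be reported to the study center and the board and still be absent from the listed rates, provided the patient neither died nor was hospitalized. What is at stake is the claim that disease course was not made worse: part of the evidence that could contradict it would not be compared between arms.

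**Working it through.** The article gives no event rates, so there is no figure to reproduce. The check is to take each kind of event in the Safety outcomes definition and ask whether Table 1, outcome 7, is certain to count it.

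| Kind of event | Reportable under Safety outcomes? | Counted under outcome 7? |
|---|---|---|
| Death | Yes | Yes, without condition |
| Hospitalization for any reason | Yes | Yes, without condition |
| Complication of a known disease, leading to hospitalization or death | Yes | Yes, as hospitalization or death |
| Complication of a known disease, non-hospitalized and non-fatal | Yes | Only if classed as unexpected |
| New acute illness, non-hospitalized and non-fatal | Yes | Only if classed as unexpected |

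The last two rows are the gap. Of these, the complication row matters more, because a new illness is less readily foreseen from the patient's diagnoses.

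The word can be read in two ways. If *unexpected* was meant loosely, for any untoward event, the last two rows are counted and nothing is lost. If it was meant as a classification, foreseeable complications are left out. The article does not say which reading applies, or who would classify.

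The consequence under the second reading can be written without assumed numbers. Let p_I and p_C be the true rates of non-hospitalized, non-fatal events in the intervention and control arms, and e_I and e_C the shares set aside as expected. Then

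listed difference = p_I(1 − e_I) − p_C(1 − e_C).

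- If e_I = e_C = e, this equals (1 − e)(p_I − p_C). A real excess is shrunk by the factor (1 − e).
- If e_I is larger than e_C, because events after a stopped drug look more foreseeable, the excess shrinks further. It changes sign when (1 − e_I)/(1 − e_C) is below p_C/p_I.

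None of these four quantities is given, so only the direction can be stated: when there is a true excess, a filter applied equally in both arms, or more heavily in the intervention arm, makes it look smaller.

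On causality, the article makes the plausible-connection judgement a joint task of the board and the PCP. No outcome in Table 1 is a rate of events judged related, and no section says that only related events are counted. The judgement is therefore not a filter on the text as it stands, but the article does not say that it has no such role.

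**The case against.** The strongest reply is that the safety comparison is much wider than the disputed phrase. Hospitalization and death carry no expectedness condition. Blood pressure, weight and, in the relevant patients, HbA1c, TSH and hemoglobin are measured in both groups at baseline, 6 and 12 months. Quality of life is patient-reported on the EQ-5D-3L and a Likert scale, and the main complaint on a visual analogue scale. Drugs readopted because of an unfavorable disease course are counted in outcome 8. The article's own example of a complication, a myocardial infarction, would usually be captured as a hospitalization or death. The meaning of *unexpected* could also sit in a full protocol that is not shown.

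Most of this stands, and it rules out several stronger readings that a reader might infer:

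- *The comparison covers only unexpected events.* It does not; hospitalization and death are listed separately and unconditionally.
- *The no-worsening hypothesis rests only on causality attribution and a filtered count.* It does not; the biometric, laboratory and patient-reported measures also inform it.
- *Attribution removes events from the count, or is possible only in the intervention arm.* The first is stated nowhere. The second is a reasonable inference from who applies the algorithm, but the text does not limit attribution to one arm.
- *A specific loss of power follows.* The documents give no event rates and no intracluster correlation for events, and hospitalizations and deaths cannot be set aside under outcome 7.
- *The board must adjudicate with the arm masked and without the PCP.* That is a procedural preference, and such detail may sit in a document not shown.

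The reply does not remove the mismatch itself. The point is not that a definition is missing: two sections of the same article describe the event outcome differently, and one is narrower. The other measures do not count non-hospitalized complications, and the disease-course rating comes from a PCP who knows the treatment given.

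**Conclusion.** The point holds in a limited form. Outcome 7 and the Safety outcomes definition do not agree. On a literal reading, complications and new illnesses without hospitalization or death can be left out of the listed by-arm rates when they are judged expected. This weakens one part of the evidence on the no-worsening hypothesis and, for a filter applied equally or more heavily in the intervention arm, tilts that part towards finding no harm.

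The size is unknown. It depends on how common such events are and what share would be called expected, and the documents give neither. The conclusion assumes that *unexpected* is meant as a classification; if it was meant loosely, the correction only makes the intention explicit. The documents do not support a conclusion that excess harm in general would go unseen: an excess of hospitalizations or deaths would be looked for in rates that are already listed.

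**What to change.** In Table 1, outcome 7, keep the hospitalization and death rates. Replace the rate of unexpected adverse events with rates of all adverse events meeting the Safety outcomes definition. Compare these by randomized arm, regardless of expectedness or judged causality, and report a between-arm difference with a 95% interval that allows for clustering by practice. An interval suits a hypothesis of no worsening better than a test result alone.

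Under Safety outcomes, add one sentence: the plausible-connection judgement, made jointly with a PCP who cannot be blinded, is descriptive and does not determine which events are counted. Under Disease-specific parameters, state that the PCP's rating of disease course is supportive.

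The cost is wording in three places. No new data collection is needed, because PCPs must already report these events. The downside is a broader and noisier count, since minor events unrelated to any medication change will be included.
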